##### Sub-sample

Sample size calculation for the sub-sample is based on outcomes of the choice step reaction time test, which is a good approximation for overall dynamic balance [41]. Based on unpublished data from Central Sydney Tai Chi trial,[27] an estimated standard deviation of 0.2 ms can be expected. A sample size of 88 participants from each group will detect an absolute difference of 10% in reaction time. Assuming a 10% drop out rate, a sample size of 97 per group will be sufficient to detect a 10% absolute difference in reaction time between groups with an alpha of 0.05 and with power of 80%.

###### Analysis

All data will be analysed according to intention to treat analysis. Falls data will be compared across intervention and control groups at 12-months (i.e. 48-weeks) using a negative binomial regression model [27,28].

Outcome data obtained from the study questionnaire will be used to compare groups at 48-weeks. Falls efficacy, walking self-efficacy as well as perceived neighbourhood walkability will be analysed using the Kruskal Wallis test, a non-parametric test. Levels of physical activity and physical performance data will be analysed using regression models that will compare groups at 48-weeks using baseline values as a covariate.

A cost-effectiveness evaluation will calculate the cost of the walking program per fall prevented and a cost-utility analysis, based on the AQoL, will estimate the incremental cost-utility ratio expressed in terms of $AUD per QALY gain (or loss).

Sensitivity analyses will be conducted comparing unadjusted results and results adjusted for potential confounding variables. Potential confounding variables include age, gender, and previous falls. Data from the intervention group will also be analysed to investigate any dose-response relationships between level of walking and falls, and level of walking and physical performance.

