**Figure 2 F2:**
[figure not shown]
**Flowchart of participants through the study**.

Intervention group participants will record the duration and frequency of walking, on their falls calendar. Although not a compulsory part of the program, these participants will also be encouraged to use a pedometer mainly as a motivational tool to encourage participants to keep walking. Participants can do this by comparing how many steps they have taken during their walking program towards a previously set goal. The pedometer used will be the Yamax Digiwalker SW-200 pedometer, which has been successfully used to promote walking in community dwelling adults [26].

The control group will receive health information over the duration of the study (48-weeks) covering health issues such as mental health wellbeing, healthy eating and developing good sleeping habits. Control group participants will be given no instruction on physical activity during the study, after which they also receive the walking kit. Control group participants will be sent a control group study kit consisting of a falls calendar and printed material on a health topic. Information on a new health topic will be mailed out at 12-weeks and 24-weeks in parallel with the intervention group. (See Figure 2)

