#### Outcome measures

The main outcome measure is falls over the 12-month study period. A fall is defined as *'Unintentionally coming to rest on the ground, floor, or other lower level' *[27,28]. Falls will be recorded on a falls calendar, a method used successfully in previous falls prevention studies [27]. Each fall will be followed up with a telephone call by a research assistant to confirm the fall and to ascertain the circumstances around the fall including whether the fall resulted in any injuries, what treatment was sought.

Secondary outcome measures include:

• Dynamic balance and strength (sub-sample only)

• Physical performance (sub-sample only)

• Quality of life

• Walking behaviour

Other measures will be collected through the initial screening and baseline questionnaire and include basic demographic information, falls history, falls efficacy, self-reported levels of physical activity, walking self-efficacy and perceived neighbourhood walkability.

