#### Sample size

Previous falls prevention studies involving physical activity have shown a relative reduction of falls of between 20-35% [6]. Over a 12-month period it is expected that 33% of older people aged 65 years and older will fall at least once [6]. This study is powered at the alpha = 0.05 level with 80% power. A sample size of 232 per group is required to detect a relative reduction in falls of 35% (RR = 0.65) over 12-months. Adjusting the sample size to accommodate a 10% drop-out rate this study will need a sample size of 242 per group.

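### The sample size applies a 12-month faller risk to a 48-week count, so 232 evaluable per group gives about 75–76% power on the plan's own method, not 80%

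*Protocol article*

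**What the plan says.** The main outcome is given in months. Under Outcome measures: "The main outcome measure is falls over the 12-month study period".

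The operative duration is given in weeks. The Intervention section runs the walking programme over 12 months, with 48 weeks in brackets as its equivalent, and its three phases end at week 48. For the comparison arm the same section says: "The control group will receive health information over the duration of the study (48-weeks"). It then says: "Control group participants will be given no instruction on physical activity during the study, after which they also receive the walking kit".

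The Analysis section fixes the falls comparison at the same point and states the equivalence outright: "Falls data will be compared across intervention and control groups at 12-months (i.e. 48-weeks) using a negative binomial regression model".

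The Sample size section works only in months. Its control risk is "Over a 12-month period it is expected that 33% of older people aged 65 years and older will fall at least once". Its target is: "A sample size of 232 per group is required to detect a relative reduction in falls of 35% (RR = 0.65) over 12-months". On error rates it says: "This study is powered at the alpha = 0.05 level with 80% power". It does not mention 48 weeks.

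**The concern.** Forty-eight weeks is 29 days short of a year. As a label this would be harmless, but here it feeds a number. The 33% that drives the sample size is a risk over a full 12 months, while the falls that will be compared accrue over 48 weeks. Fewer people will have fallen by then, so the same number of participants yields less information than the calculation assumes.

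The stated 80% power is at stake. The protocol's Discussion gives weight to a finding that walking does not reduce falls, so the chance of missing a true effect should be stated correctly. A reader who meets 12 months in one section and 48 weeks in another also has to work out on which day counting stops.

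**Working it through.** **Inputs**
- Control risk 33% with at least one fall, over 12 months (Sample size).
- Risk ratio 0.65, so 0.33 × 0.65 = 21.45% in the walking group (Sample size).
- Alpha 0.05 and power 80% (Sample size). Sidedness is not stated; two-sided is taken because it reproduces the stated figure, whereas one-sided gives 183 per group.
- 232 per group before drop-out, 242 after (Sample size).
- Counting window 48 weeks (Analysis; Intervention).

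**Step 1: reproduce the stated figure.** Two proportions, pooled variance, no continuity correction, with p̄ the mean of p₁ and p₂ and each q = 1 − p:

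n = [1.960·√(2p̄q̄) + 0.842·√(p₁q₁ + p₂q₂)]² / (p₁ − p₂)²

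With p₁ = 0.33, p₂ = 0.2145 and p̄ = 0.27225, the two roots are 0.6295 and 0.6242. Then n = (1.2338 + 0.5253)² / 0.1155² = 3.0944 / 0.01334 ≈ 232. The stated figure is reproduced, so the 12-month 33% is what drives it. Power at 232 is 80.0%.

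**Step 2: the window.** 48 × 7 = 336 days; 336/365 = 0.921 of a year, or 11.05 months.

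**Step 3: rescale the risk.** The documents give no 48-week risk, so two simple assumptions set the range:
- Constant hazard: 1 − (1 − 0.33)^0.921 = 30.8%.
- Proportional to time: 0.33 × 0.921 = 30.4%.

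**Step 4: recompute with the risk ratio held at 0.65.**
- Constant hazard: p₁ = 0.3083, p₂ = 0.2004, difference 0.10792. n = (1.2072 + 0.5144)² / 0.10792² ≈ 254.5, so 255.
- Proportional: p₁ = 0.3038, p₂ = 0.1975, difference 0.10632. n = (1.2012 + 0.5119)² / 0.10632² ≈ 259.6, so 260.

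Power at n per group is Φ{[(p₁ − p₂)√n − 1.960·√(2p̄q̄)] / √(p₁q₁ + p₂q₂)}. At n = 232, constant hazard gives (1.6438 − 1.2072)/0.6112 = 0.714, or 76.3%. Proportional rescaling gives 0.688, or 75.4%.

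| Control risk | n per group for 80% | Power at 232 | Power if all 242 are evaluable |
|---|---|---|---|
| 33% (as planned) | 232 | 80.0% | 81.6% |
| 30.8% (constant hazard) | 255 | 76.3% | 78.0% |
| 30.4% (proportional) | 260 | 75.4% | 77.2% |

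The requirement rises by 10–12% (255/232 = 1.10; 260/232 = 1.12). Power at 232 falls by 3.7 to 4.6 points. Even with every one of the 242 evaluable, power stays below 80%.

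**The case against.** The strongest reply is that this is loose labelling. The protocol states its convention more than once, the 12-month study period is that same 48-week period, and the Analysis section fixes the comparison there. That stands as far as the intended window goes: 48 weeks is the natural reading. It does not rescue the sample size, because the 33% is stated for a 12-month period and is used unadjusted.

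A second reply is that the planned analysis is negative binomial regression, whose power depends on a fall rate and a dispersion that the sample-size paragraph does not give. This also stands: the 75–76% describes the two-proportion approximation only. But that approximation is the plan's own basis for claiming 80%, and a count model too would see about 8% less person-time (1 − 0.921). It is fair to add that 33% is a general figure for people aged 65 and over, so a shift of about two points is a small refinement of an already approximate assumption.

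Two stronger readings are tempting and should not be drawn.
- A reader might infer that the last four weeks of a calendar year would compare walkers with controls who already hold the walking kit. The documents do not support this. No passage plans to count falls to day 365, and the kit goes out only after the study, with no date or lag given. Contamination would require a 48-week study for the kit and a 52-week study for the count, a combination that the text never states.
- A reader might add drop-out to the loss. Taking 10% from 242 leaves about 218 per group, but power there is already 77.5% at the unadjusted 33%. That shortfall comes from the separate step from 232 to 242 and is not an effect of the window.

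**Conclusion.** The point holds as a mismatch between the period of the planning risk and the period of the count. On the plan's own calculation, 232 evaluable per group gives about 75–76% power over 48 weeks instead of 80%, and 255–260 per group would be needed to keep 80%. The loss is modest, about 4–5 points.

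This rests on a constant hazard or proportional rescaling of the 33%, on an unchanged risk ratio of 0.65, and on a two-sided test. It is not a statement about the power of the negative binomial model. It implies no bias: both arms are followed for the same 48 weeks, so the rate ratio remains valid. Nor do the documents show that contamination of the control group is planned.

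**What to change.** - Define the primary outcome as falls from randomisation to day 336 (48 weeks) in both arms. Use that window in the Outcome measures, Sample size and Analysis sections in place of 12 months.
- In the Sample size section, replace 33% by about 31% (30.8%), say that it is the 12-month figure rescaled to 48 weeks under a constant hazard, and restate the power as about 76% at 232 evaluable per group.
- State that falls after day 336 are not counted. The count then ends before controls receive the walking kit, and the question of overlap does not arise.

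The cost is wording and a slightly less favourable power figure. No additional enrolment, follow-up or data collection is asked for.

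### Three ancillary questionnaire scales are compared at 48 weeks by a Kruskal-Wallis test that ignores baseline scores already collected, while the same paragraph baseline-adjusts activity and performance

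*Protocol article*

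**What the plan says.** The Analysis section compares groups on the study questionnaire at 48 weeks. For three of its scales it fixes the method: "Falls efficacy, walking self-efficacy as well as perceived neighbourhood walkability will be analysed using the Kruskal Wallis test, a non-parametric test". The sentence that follows treats levels of physical activity and physical performance differently, by "regression models that will compare groups at 48-weeks using baseline values as a covariate".

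The three scales are available at baseline. The Outcome measures section says: "Other measures will be collected through the initial screening and baseline questionnaire and include basic demographic information, falls history, falls efficacy", and the same list goes on to walking self-efficacy and perceived walkability. Recruitment and randomization places allocation after the baseline interview, so these scores precede randomisation. They appear after, and apart from, the four listed secondary outcomes.

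For falls, the main outcome, the Analysis section names a negative binomial model and mentions no covariate beside it. Adjustment comes later: "Sensitivity analyses will be conducted comparing unadjusted results and results adjusted for potential confounding variables". Age, gender and previous falls are the variables given. The Falls History and Falls Efficacy section records the number of falls in the 12 months before the baseline interview.

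**The concern.** With two arms, Kruskal-Wallis is a rank-sum test of the 48-week scores. It cannot use a participant's own starting score, which for a repeated questionnaire scale is usually the strongest available predictor of the later one. Any chance difference between arms at baseline stays in the comparison, and the test alone gives a p-value without an effect size or interval.

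The plan is also inconsistent within one paragraph. Self-reported activity comes from the same study questionnaire as the three scales, yet it is adjusted for baseline and they are not. No reason is given. What is at stake is precision and interpretability for three ancillary measures; the validity of the test is not in doubt.

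A lesser question of the same kind arises for falls. Prior falls, age and gender are known for everyone before randomisation, but they enter only through a sensitivity analysis that calls them potential confounders. In a randomised trial their main use is to gain precision.

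**Working it through.** **1. The plan's own figure.** The Sample size section gives: "This study is powered at the alpha = 0.05 level with 80% power"; "Over a 12-month period it is expected that 33% of older people aged 65 years and older will fall at least once"; "A sample size of 232 per group is required to detect a relative reduction in falls of 35% (RR = 0.65) over 12-months". So p1 = 0.33, p2 = 0.33 × 0.65 = 0.2145, and the mean is 0.27225. Sidedness is not stated; two-sided is taken here.

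n = [1.960·√(2 × 0.27225 × 0.72775) + 0.842·√(0.33 × 0.67 + 0.2145 × 0.7855)]² / (0.1155)² = 231.96, so 232 per group.

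This matches exactly. No covariate enters it, and it concerns falls, so the three scales have no sample size of their own. The recruitment target is 242 per group with 10% drop-out: "Adjusting the sample size to accommodate a 10% drop-out rate this study will need a sample size of 242 per group". 242 × 0.9 = 217.8, taken as 218 per group below.

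**2. Gain for the scales.** With baseline-to-48-week correlation ρ, baseline adjustment multiplies the residual variance by 1 − ρ². Power for a standardised effect d with n per group is approximately Φ( d·√(n/2)/√(1 − ρ²) − 1.96 ). Neither ρ nor d is in the documents; ρ = 0.3 to 0.7 and d = 0.2 SD are assumptions. With n = 218, d·√(n/2) = 0.2 × √109 = 2.088.

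| ρ | 1 − ρ² | Fall in variance | SE ratio | Power at 0.2 SD |
|---|---|---|---|---|
| unadjusted | 1 | – | 1 | 55% |
| 0.3 | 0.91 | 9% | 0.954 | 59% |
| 0.5 | 0.75 | 25% | 0.866 | 67% |
| 0.7 | 0.51 | 49% | 0.714 | 83% |

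The same factors would lift a comparison that has 80% power to about 84%, 90% and 98%.

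**3. Check on ranks.** The formula is for means, so Kruskal-Wallis and rank ANCOVA were compared directly by simulation: 218 per arm, a shift of 0.275 SD (chosen to give about 80% power), 2,000 trials per case.

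| ρ | Kruskal-Wallis (normal / skewed) | Rank ANCOVA (normal / skewed) |
|---|---|---|
| 0.3 | 80.5% / 79.2% | 83.0% / 82.1% |
| 0.5 | 78.7% / 80.1% | 88.7% / 90.3% |
| 0.7 | 78.9% / 79.9% | 97.2% / 96.9% |

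The skewed scores are exponentials of normal ones. That leaves ranks unchanged, so the two sets should agree up to simulation noise, and they do. Rank ANCOVA keeps the protection against skew and still uses baseline.

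**4. Gain for falls.** The documents give no mean fall rate, dispersion or prior-faller rate ratio, so these are all assumed. Two sets of simulations used a true rate ratio of 0.65, 218 per arm and 33% prior fallers.

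- Prior fallers at 2 to 3 times the rate, 400 trials per scenario: the median SE of the log rate ratio went from 0.179 to 0.177, 0.182 to 0.176 and 0.182 to 0.173, which are cuts of 1.1%, 3.3% and 4.9%. Power went from 67.5% to 70.8%, 64.8% to 68.0% and 64.3% to 68.0%.
- Control mean 0.45 or 0.7 falls per year, prior-faller rate ratio 1.5 to 2.8, dispersion 0.5 or 1.0, about 300 trials per scenario: the model-based variance ratio was 0.90 to 0.99, so the SE fell by about 0.5% to 5%. The power change ran from −0.7 points (83.0% to 82.3%) to +6.0 points (77.0% to 83.0%).

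Each simulated power carries a standard error of about 2 to 3 points, so the small changes are within noise. In the first scenario the SE change alone implies only about 1 point: |ln 0.65| = 0.431, and Φ(0.431/0.179 − 1.96) = 0.67 against Φ(0.431/0.177 − 1.96) = 0.68.

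**The case against.** The strongest reply is that the plan uses baseline where its aims need it. Physical activity and physical performance serve the second aim and the listed secondary outcomes, and both are baseline-adjusted. Falls efficacy, walking self-efficacy and walkability appear in neither aim and carry no sample size. A reader might infer that key comparisons are affected; for the scales, the documents do not support that.

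A rank test is also a reasonable guard against skewed or ordinal scores such as five-point Likert items, so it would be wrong to infer that the precision is given up for no return. That stands as a reason for using ranks. It is not a reason for leaving baseline out, because rank ANCOVA and ordinal models offer similar protection.

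On falls, a reader might infer that the main analysis is defective, or that neither falls estimate is designated as the main one. Neither follows. An unadjusted negative binomial comparison is valid in a randomised trial. The adjusted analysis is already planned, so chance imbalance in prior falls will be examined. Since adjustment sits under sensitivity analyses, the natural reading is that the unadjusted model is the main one. That is still an inference, because the article never calls it unadjusted, and a condensed article may leave covariates to a fuller plan. Near-zero gain is within the assumed range for falls. What remains is a preference about which of two planned analyses leads.

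**Conclusion.** The point holds for the three scales as a loss of efficiency on ancillary outcomes. The test is fixed explicitly, it ignores scores that will be in hand, and it is inconsistent with the next sentence of the same paragraph. The gain from adjustment is about 9% to 49% of residual variance if ρ is 0.3 to 0.7, or power of about 59% to 83% in place of 55% for a 0.2 SD effect with 218 per group. Both the correlation and the effect size are assumptions, so the direction is secure and the size is not.

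The falls part is secondary and minor: SE down by about 1% to 5% and power up by about 0 to 6 points, depending on assumed fall rates, dispersion and prior-faller effect. Nothing here shows bias or an invalid analysis for any outcome.

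**What to change.** For falls efficacy, walking self-efficacy and perceived walkability, replace the Kruskal-Wallis test with a regression of the 48-week score on group and baseline score. If scores are skewed, use rank ANCOVA or a proportional-odds model with baseline as a covariate. Report the adjusted effect with a 95% CI where the method gives one: linear regression and the proportional-odds model do so directly, whereas rank ANCOVA mainly gives a test. Fix the rule for choosing among them before group comparisons are seen.

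Optionally, name the negative binomial model adjusted for prior falls, age and gender as the primary falls analysis, describe these as precision covariates, close the list, and keep the unadjusted model as the sensitivity analysis.

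Both changes are to analysis wording only. The covariates are already collected before randomisation, so no visit, instrument or participant is added.

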## Discussion

Walking has been shown to have many health benefits, even later in life. For example, older men and women who walked regularly have reduced risk of all cause mortality, [42] of developing cardiovascular disease, [43] of cognitive decline, [44] and functional limitations [45]. Among postmenopausal women, adherence to walking regimens was associated with improved bone mass density,[46] favorable changes in blood lipids and glucose tolerance,[47] and reduced hypertension [48].

In a meta-analysis of exercise interventions to prevent falls, studies of exercise programs which included walking programs had lesser fall prevention effects than exercise programs that did not include walking programs. The authors suggest that the effect of walking may be cofounded by the tendency to prescribe walking regimens in trials involving high-risk population. Further, it was postulated that multi-component programs (e.g. balance, and walking) might be less efficient if time devoted to the most beneficial component, which is balance training, is compromised [7]. This study addresses these questions. It recruits community-dwelling older people not based on their falls risk, and it prescribes only walking with no other competing activity that can dilute or enhance the effect.

Despite evidence showing that certain types of physical activity reduce the risk of falls there still remain significant barriers for older people to become more active. In an effort to increase activity levels public health recommendations highlight the metabolic and cardiovascular benefits of accumulated daily day activity as long as it is of moderate-intensity. This includes household chores, gardening and walking. The role of lifestyle physical activity in relation to falls risk is under-studied. In this respect our study will be the first to determine if accumulated daily episodes of walking in older people's environments is also beneficial for falls.

Walking potentially overcomes many barriers for regular active lifestyle. It is already the most popular physical activity amongst older people requiring no training or special equipment. Most importantly, it is free. If walking is shown to reduce falls the public health implications could be enormous. Conversely, if walking does not reduce falls in older people, or even if it puts older people at greater risk then health resources targeting falls prevention would need to address those who choose walking as their single form of exercise, to increase their protection. This could be done by reducing falls hazards in the environment and by educating walkers of the need to maintain good balance before starting walking regimens and providing examples of simple home-based balance enhancing exercises.
